# Differences in the individual curative effect of acupuncture for obese women with polycystic ovary syndrome based on metagenomic analysis: study protocol for a randomized controlled trial

**DOI:** 10.1186/s13063-021-05426-y

**Published:** 2021-07-15

**Keywords:** Acupuncture, Obesity, Polycystic ovary syndrome, Gut microbiota, Protocol

## Abstract

**Background:**

Polycystic ovary syndrome is a common cause of infertility and shows a high incidence in women of reproductive age. Acupuncture is an appropriate adjunctive treatment for PCOS. However, the add-on effect of acupuncture as an adjunctive treatment for obese women with PCOS has not been studied, and previous studies indicate that there are individual differences in the curative effect of acupuncture, while deeper research on the mechanism of differences in the individual curative effect of acupuncture for obese women with PCOS is still lacking. This trial aims to assess the add-on treatment efficacy of acupuncture for obese women with PCOS and to explore the role of the gut microbiome on the differences in the individual curative effect of acupuncture based on metagenomic analysis.

**Methods/design:**

This is an open-label, randomized, controlled trial. A total of 86 obese women with PCOS will be recruited. Subjects will be randomly assigned to a study group and a control group in a 1:1 ratio, with 43 subjects in each group (10 patients from each group who meet the study criteria will participate in the metagenomic analysis). An additional 10 subjects who meet the study criteria will be recruited to a healthy control group. The study group will receive acupuncture and clomiphene citrate treatment; the control group will only receive clomiphene citrate. Acupuncture treatment will be conducted three times a week from the fifth day of menstruation or withdrawal bleeding until the start of the next menstruation, for up to three menstrual cycles. The primary outcome will be LH/FSH. The secondary outcomes will comprise biometric features, hormone biomarkers, metabolic biomarkers, inflammatory biomarkers, Self-Rating Anxiety Scale, Self-Rating Depression Scale, and metagenomic analysis. The outcomes will be measured at baseline and post-intervention. Data will be analyzed using SPSS 19.0, and the gut microbiome will be analyzed using metagenomic analysis.

**Discussion:**

In this study, we are evaluating the add-on effects of acupuncture and exploring the mechanism of the differences in the individual curative effect of acupuncture based on the gut microbiome, which may provide evidence to explain the different outcomes of different trials on acupuncture for PCOS and hopefully to provide a new aspect to study the mechanism of acupuncture’s treatment effect.

**Trial registration:**

Chinese Clinical Trial Registry ChiCTR2000029882. Registered on 16 February 2020

**Supplementary Information:**

The online version contains supplementary material available at 10.1186/s13063-021-05426-y.

## Background

Polycystic ovary syndrome (PCOS) is a common endocrine and metabolic disorder characterized by androgen excess (hirsutism and/or hyperandrogenemia) and ovarian dysfunction (oligo-ovulation and/or polycystic ovarian morphology) [1]. The estimated prevalence of PCOS varies from 5 to 20% in women of reproductive age [2–8], and about 50% of PCOS cases are associated with obesity [9]. As one of the most common causes of subfertility, PCOS accounts for 30 to 40% of infertility and 75% of anovulatory infertility [10]. The increasing prevalence of obesity has an important bearing on the PCOS phenotype [11, 12], and women diagnosed with PCOS who have higher body mass index (BMI) are more likely to have menstrual irregularity, hyperandrogenemia, hirsutism, and insulin resistance [13–15], which can exacerbate the reproductive and metabolic abnormalities of PCOS [16]. Obese women with PCOS are more likely to experience psychological disorders, such as depression and anxiety [17], and babies born to women with PCOS may have increased morbidity and mortality [15], which can be a big burden for both patients and the healthcare system.

Clomiphene citrate, as the first-line ovulation induction drug, has been used among infertile PCOS women with fertility desires for decades. However, from a clinical point of view, the current management of PCOS with this drug is not always satisfactory and produces some obvious side effects [18]. After taking clomiphene citrate, 39.22% of women still failed to ovulate. The live birth rate for these patients was only 7.84% after taking clomiphene citrate. Other side effects include gastrointestinal symptoms, hot flashes, headache, fatigue, abdominal cramping, and symptoms associated with ovarian enlargement and ovulation [19, 20]. Thus, an increasing number of patients with PCOS are seeking complementary and alternative medicine (CAM) methods such as acupuncture for fertility assistance [21, 22].

Acupuncture, as a part of CAM, has been long used to treat PCOS. Although researches have shown that acupuncture can activate the neural-endocrine-immune network and increase beta-endorphin production to balance the endocrine system and hormones, as well as affect ovulation and menstrual cycle, evidence for acupuncture’s utility for PCOS is conflicting [23–30]. Findings from previous clinical studies suggest acupuncture may induce ovulation [27], improve menstrual frequency, and decrease the levels of several sex steroids [28]. Additionally, the low associated adverse event rate, a low risk of multiple pregnancies, and the low cost of acupuncture have been noted [31]. Nevertheless, the methodological quality of these clinical trials varies, resulting in inconclusive statements on the effectiveness of acupuncture for PCOS. Meanwhile, the add-on effect of acupuncture as an adjunctive treatment for obese women with PCOS has not been studied, although acupuncture has shown some efficacy in managing PCOS, especially in conjunction with pharmaceutical treatments [26].

Furthermore, a study found a higher ovulation rate in the active acupuncture group than in the clomiphene alone group, but the results indicated that acupuncture did not affect the live birth rate [32]. Another study also found an improvement in the ratio of luteinizing hormone (LH) to follicle-stimulating hormone (FSH) during the 8 weeks of intervention, and this persisted for 3 months of follow-up in the acupuncture arm; however, there was no difference in ovulation rate between the true acupuncture group and the sham acupuncture group over 5 months [33]. Given these contrasting findings, we hypothesize that the curative effect of acupuncture for PCOS is associated with individual differences, that is, whether patients show sensitivity to acupuncture is one of the differences in the individual curative effect of acupuncture. However, the cause of differences in the individual curative effect of acupuncture for obese women with PCOS has not yet been studied.

Recently, there has been an explosion of interest in the study of the gut microbiome and its impact on host health and physiology [34]. The gut microbiome comprises the collective genome of the trillions of microorganisms residing in our gastrointestinal ecosystem [35]. The composition and activity of the gut microbiome have a substantial effect on human health and are regarded as the main cause of individual differences [36]. Studies have shown that the gut microbiome is strongly associated with PCOS, as well as the development and clinical parameters of PCOS. Studies have pointed out that the stool microbiome of PCOS patients shows a lower alpha diversity [37–41]; the relative abundance of bacteria from the phylum Tenericutes, the order ML615J-28 (phylum Tenericutes), and the family S24-7 (phylum Bacteroidetes) is significantly lower than health controls [37]. Besides, researches indicate that the gut microbiota-bile acid interleukin-22 axis or the brain-gut axis may be the potential mechanism in the development progress of PCOS, and the dysbiosis of the gut microbiota is strongly relevant to endocrine disorders, including LH, FSH, LH/FSH, anti-Mullerian hormone (AMH), and testosterone, in PCOS patients [38, 42–44]. Of note, the gut microbiome also plays an important role in the curative effect of acupuncture. Acupuncture research has demonstrated that acupuncture can regulate the brain-gut-bacteria axis and reverse disturbances in the gut microbiota metabolism [45, 46]. Electro-acupuncture treatment can normalize several chronic atrophic gastritis (CAG)-induced metabolomic changes by partially reversing CAG-induced disturbances in the gut microbiota metabolism [46]. As gut microbiota is a major target for diseases’ treatment and may predict responses to clinical therapy [47], as well as it is strongly associated with PCOS and the curative effect of acupuncture, thus, we speculate that acupuncture might play a therapeutic role in women with PCOS by regulating the gut microbiome, and the gut microbiome may be strongly associated with the differences in the individual curative effect of acupuncture for obese women with PCOS.

Considering that the add-on effect of acupuncture as an adjunctive treatment for obese women with PCOS has not been studied, and acupuncture for obese women with PCOS may exist individual curative effect differences, we designed this randomized controlled trial (RCT) to evaluate the add-on effects of acupuncture to conventional drugs in obese women with PCOS, as well as to investigate the mechanism of differences in the individual curative effect of acupuncture for obese women with PCOS by using metagenomic analysis method.

## Methods/design

### Study design

This will be an open-label, randomized, controlled trial. The study will recruit 86 obese patients with PCOS from Sichuan Women’s and Children’s Hospital, Sichuan Provincial Hospital of Traditional Chinese Medicine, the Third Affiliated Hospital of Chengdu University of Traditional Chinese Medicine, or Xinan Women’s and Children’s Hospital. The patients enrolled will be randomly assigned to a study group or a control group. The allocation ratio is 1:1, with 43 subjects in each group. All patients involved in this trial will be asked to sign the consent form before the intervention by researchers. Patients in the study group will be given acupuncture and clomiphene citrate treatment, and the control group will receive only clomiphene citrate treatment.

In addition, with the purpose to explore the mechanism of the differences in the individual curative effect of acupuncture, 10 subjects from each group will be selected in the order of enrollment for the metagenomic analysis. The selection criteria for these 10 subjects from each group will be that 5 of them with post-intervention LH/FSH levels of 1.0–1.5 and the other 5 subjects with post-intervention LH/FSH levels over 1.5. Meanwhile, ten healthy subjects who meet the study criteria will be recruited as the healthy control group and will not be given any intervention. The flow chart of the trial process is shown in Fig. 1. The research data collection is described in detail in Table 1.

### Participants

#### Recruitment

Participants will be recruited from the gynecological outpatient departments of Sichuan Women’s and Children’s Hospital, Sichuan Provincial Hospital of Traditional Chinese Medicine, the Third Affiliated Hospital of Chengdu University of Traditional Chinese Medicine, or Xinan Women’s and Children’s Hospital. Recruitment posters, advertisements, and internet advertisements will be used to recruit participants. Before participation, patients will be informed about the study design, the advantages and disadvantages of the treatment, and the relevant safety measures that will be used during the trial.

#### Inclusion criteria

##### Inclusion criteria for PCOS

PCOS diagnosis will be based on the *Revised 2003 Consensus on Diagnostic Criteria and Long-Term Health Risks related to Polycystic Ovary Syndrome* established by the Rotterdam ESHRE/ASRM-Sponsored PCOS Consensus Workshop Group [51]. According to the criteria, women with two or three of the following symptoms can be diagnosed with PCOS: hyperandrogenism, ovulatory dysfunction (oligo-ovulation or anovulation), and polycystic ovary morphology based on ultrasound.

The inclusion criteria are as follows: (1) infertile female with reproductive needs aged 20 to 40 years, (2) meets the diagnostic criteria for PCOS, (3) BMI ≥ 25 kg/m^2^, (4) suitable for administration of clomiphene as an ovulation induction treatment, and (5) has signed an informed consent form.

##### Inclusion criteria for healthy participants

The inclusion criteria for healthy participants are as follows: (1) female patient aged 20 to 40 years, (2) BMI ≥ 18.5 kg/m^2^ and ≤ 25 kg/m^2^, (3) with regular menstruation, (4) no primary dysmenorrhea history in the past years, (5) normal blood/stool/urine test, (6) no mental illness, and (7) has signed an informed consent form.

#### Exclusion criteria

##### Exclusion criteria for PCOS

Subjects will be excluded if they have any of following conditions: (1) patient does not meet the diagnostic criteria for PCOS; (2) with history of taking antibiotics in the past 3 months; (3) with allergic condition; (4) with conditions such as hyperandrogenism due to hyperprolactinemia, thyroid disease, congenital adrenal hyperplasia, and Cushing syndrome; (5) with pathological endometrial changes, such as uterine malformation and hysteromyoma diagnosed using ultrasound; (6) with conditions such as genital tract malformation, gonadal dysgenesis, and fallopian tube blockage; (7) with severe heart, liver, or renal dysfunction; or hematological, respiratory, cardiovascular, and psychiatric; (8) patient has participated in other clinical trials; (9) patients with gastrointestinal surgery history; (10) patient has smoking history, alcohol use history, inflammatory bowel disease, irritable bowel syndrome, autoimmune diseases, cancer, or any other diseases that may influence the gut microbiome; (11) patient has probiotics taking history within 1 month; (12) with uncontrolled disease(s) that cause inflammation; and (13) patient has diagnosed with anxiety or depression.

Items from (1) to (8) are suitable for clinical observation. Items from (1) to (13) are suitable for metagenomic analysis.

##### Exclusion criteria for healthy participants

Healthy participants with any of the following conditions will be excluded from this study: (1) with antibiotics taking history in the past 3 months; (2) with smoking history and/or alcohol use; (3) with mental disorders, cognitive disorders, or allergic conditions; (4) patient is pregnant or lactating; (5) with gastrointestinal surgery history; (6) with inflammatory bowel disease, irritable bowel syndrome, autoimmune diseases, cancer, or other diseases that may influence the gut microbiome; (7) with probiotics taking history within 1 month; (8) with uncontrolled disease(s) that cause inflammation; and (9) patient has participated in other clinical trials.

### Intervention

All participants will be informed of the benefits of healthy lifestyle habits, such as regular exercise and healthy eating. The study group will receive acupuncture and clomiphene citrate treatment; the control group will receive only clomiphene citrate. The intervention in both groups will last three menstrual cycles. Acupuncture treatments will be given by professional acupuncturists with at least 2 years of practical acupuncture experience.

#### Acupuncture treatment

Acupuncture points will be selected based on the Zang-fu organ system, Yin-Yang theory, and clinical rules for PCOS acupoint selection. Two sets of acupoints will be used; each set will be used on alternate treatments. The first acupoint formula comprises DU-20, DU-24, GB-13, RN-12, ST-25, RN-4, EX-CA-1, KI-12, SP-6, and LR-3. The second acupoint formula comprises BL-23, BL-32, SP-6, and KI-3. Disposable, single-use, sterilized needles (Huatuo, Suzhou Medical Appliance Fact. 215005 Suzhou, China) of sizes 0.25 mm × 25 mm, 0.25 mm × 40 mm, and 0.25 mm × 50 mm will be inserted into the acupoints, and a *Deqi* sensation obtained by manipulating the needles. Table 2 shows the location, depth, and type of insertion for each acupoint. Each treatment will last for 30 min; no manipulation will be used once the *Deqi* sensation is achieved. The acupuncture treatment will be conducted three times a week from the fifth day of menstruation or withdrawal bleeding until the start of the next menstruation, for up to three menstrual cycles.

**Table 2 Tab2:** Acupuncture protocol

Acupoints	Location	Method
**Set 1**		
DU-20 (Baihui)	On the head, 5*cun* directly above the midpoint of the anterior hairline	0.5–1.0*cun* subcutaneous insertion
DU-24 (Shenting)	On the head, 0.5*cun* directly above the midpoint of the anterior hairline	0.5–1.0*cun* subcutaneous insertion
GB-13 (bilateral) (Benshen)	On the head, 0.5*cun* within the front hairline, 3*cun* from Shenting (GV-24)	0.5–1.0*cun* subcutaneous insertion
RN-12 (Zhongwan)	On the anterior median line of the upper abdomen, 4*cun* below the navel	1.0–1.5*cun* perpendicularly insertion
ST-25 (bilateral) (Tianshu)	On the middle portion of the abdomen, 2*cun* lateral to the center of the navel	1.0–1.5*cun* perpendicularly insertion
RN-4 (Guanyuan)	On the anterior median line of the lower abdomen, 3*cun* below the navel	1.0–1.5*cun* perpendicularly insertion
EX-CA-1 (bilateral) (Zigong)	On the lower abdomen, 4*cun* below the navel, 3*cun* lateral to Zhongji (RN-3)	1.0–1.5*cun* perpendicularly insertion
KI-12 (bilateral) (Dahe)	On the lower abdomen, 4*cun* below the center of the navel, 0.5*cun* lateral to the anterior midline	1.0–1.5*cun* perpendicularly insertion
SP-6 (bilateral) (Sanyinjiao)	On the medial side of the shank, 3*cun* above the medial malleolus, by the posterior of the tibia	1.0–1.5*cun* perpendicularly insertion
LR-3 (bilateral) (Taichong)	On the dorsum of the foot, in the depression proximal to the first metatarsal space	1.0–1.5*cun* perpendicularly insertion
**Set 2**		
BL-23 (bilateral) (Shenshu)	On the lower back, 1.5*cun* lateral to the lower border of the spinous process of the 2nd lumber vertebra	0.5–1.0*cun* perpendicularly insertion
BL-32 (bilateral) (Ciliao)	In the region of the sacrum, between the posterior superior iliac spine and the posterior median line, in the 2nd posterior sacral foramen	2.5–3.0*cun* oblique insertion to the 2nd posterior sacral foramen
SP-6 (bilateral) (Sanyinjiao)	On the medial side of the shank, 3*cun* above the medial malleolus, by the posterior of the tibia	1.0–1.5*cun* perpendicularly insertion
KI-3 (bilateral) (Taixi)	On the medial side of the foot, posterior to the medial malleolus, in the depression between the tip of the medial malleolus and the tendon calcaneus	0.5–1.0*cun* perpendicularly insertion

*Note*: Two sets of acupoints will be used; each set will be used on alternate treatments

#### Clomiphene citrate treatment

Clomiphene citrate treatment will be administered on the fifth day of menstruation to participants without amenorrhea in the study and control groups. Participants will receive treatment with an initial oral dose of 50 mg for 5 continuous days. If there is an ovulatory response, this dose will be maintained and will be given on the next cycle. For patients with no ovulatory response, an additional 50 mg dose will be given on the next cycle; the maximum dose of clomiphene citrate will not exceed 150 mg. Patients with amenorrhea will receive the same pharmacological treatment regimen after withdrawal bleeding has been induced by progestin. The treatment will last for three menstrual cycles.

### Outcome measures

#### Primary outcome

The primary outcome will be the change of LH/FSH. Data will be collected before the start of the study (the baseline assessment) and after 3 menstrual cycle treatments.

#### Secondary outcomes

The secondary outcomes will include changes in biometric features, changes in hormonal parameters/metabolic parameters/inflammatory parameters, changes in Self-Rating Anxiety Scale (SAS) and Self-Rating Depression Scale (SDS) scores, and changes in gut microbiome analysis. Data will be collected before the start of the study and after 3 menstrual cycle treatments.

Biometric features related to obesity, including BMI and waist will be assessed. BMI will be calculated in kg/m^2^. Waist circumference will be measured as the smallest circumference between the lowest rib and the iliac crest [52, 53]. Blood samples to assess hormonal parameters, metabolic parameters, and inflammatory parameters will be collected in the morning after an overnight fast, on day 3 of a menstrual cycle. Sex hormonal parameters will include FSH, LH, total testosterone, progesterone, and estradiol. The adipocyte-secreted hormone will be assessed by leptin, which was discovered in 1994 and can cause abnormal energy homeostasis and profound obesity [54, 55]. Leptin circulates primarily at levels proportional to the amount of adipose tissue, signaling long-term energy storage, and secondarily at levels modified by acute changes in caloric intake [56]. Leptin should decrease weight when circulating at high levels [57], and it plays a clear role in obesity etiology [58]. The metabolic parameters will include fasting blood glucose (FBG), fasting insulin (FINS), homeostatic model assessment for insulin resistance (HOMA-IR), c-peptide release tests, total cholesterol (TC), triglycerides (TG), high-density lipoprotein (HDL-C), and low-density lipoprotein (LDL-C). HOMA-IR will be calculated using the following formula: FBG (mmol/L) × FINS (mIU/L)/22.5 [59]. Inflammatory parameters will include C-reactive protein (CRP), interleukin-6 (IL-6), interleukin-18 (IL-18), and interleukin-22 (IL-22). These cytokines are related to inflammatory cytokines involved in PCOS [60–62]. SAS and SDS scores will be used to assess the patients’ mental health. The Self-Rating Anxiety Scale (SAS) and Self-Rating Depression Scale (SDS) can discriminate anxiety and depression from mood disorder and have been used continuously in research since 1972 [63, 64].

To explore the role of the gut microbiome in individual curative effect differences of acupuncture, a metagenome-wide association study (MWAS) method will be used. MWAS is a powerful tool with which to explore the microbiome and enables high-resolution investigation of associations between the human microbiome and some complex diseases. These associations are not limited to the identification of more or less abundant taxa, but also include the identification of enriched or depleted microbial functions [65]. Before the stool samples are collected, a patient involved in the metagenomic analysis will be asked to fill out a Diet and Lifestyle Habits Questionnaire. Fresh fecal samples will be collected from the participants in the morning after an overnight fast on their first visit and the end of intervention using empty stool collection tubes with an inbuilt spatula (Praxisidienst GmbH, Longuich, Germany). Their samples will be then transported to the laboratory with an ice pack within 2 h. All samples then are frozen and stored at − 80 °C before the analyses. The metagenomic analysis will be performed by BGI Shenzhen Co., Ltd. (China).

The metagenomic analysis will include 6 parts: (1) operational taxonomic units (OTUs): comparison the composition of intestinal microbiota at the level of phyla, classes, orders, families, genera, and species in each group; (2) alpha diversity: comparison the richness of species (the Chao 1 index), the abundance of the species (the Shannon-Wiener index and the Simpson index), and the evenness of the species (the Shannoneven index and the Simpsoneven index) in each group; (3) beta diversity: principal component analysis (PCA) and principal coordinate analysis (PCoA) will be used to identify the beta diversity in each group and hopefully to understand whether the differences in the microbiota compositions of groups are significant; (4) the taxonomic profile: comparison of the variety and relative abundance of taxon in the study group and control group at the level of phyla, classes, orders, families, genera, and species; (5) gene abundance profile: in order to identify the specific genes related to the individual curative effect differences of acupuncture, gene abundance will be profiled between the study group and control group, as well as within group (5 patients with post-intervention serum LH/FSH levels of 1.0–1.5 and 5 patients with serum LH/FSH levels over 1.5); (6) metagenomic biological pathways: selecting genes annotated by Kyoto Encyclopedia of Genes and Genomes (KEGG) to evaluate the functional aspects of the PCOS gut metagenome and hopefully to identify the metagenomic biological pathways contributing to the mechanism of individual curative effect differences of acupuncture for obese women with PCOS.

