### Sample size

A previous study has found an average LH/FSH ratio for patients with PCOS after true acupuncture treatment of 1.4 [33]. Thus, we expect that the average LH/FSH ratio will be 1.0 in the study group and 1.6 in the control group. Assuming a power of 80% and a significance level of 0.05, 37 participants in each group will be required, as calculated using the *t*-test in G*Power. Based on a 15% dropout rate, 86 patients will be recruited, with no less than 43 participants in each group. Since there is no standard sample size calculation for metagenomic analysis at present, according to most of the studies about gut microbial studies for PCOS [44, 66], of the 86 participants, 10 patients in each group (5 patients with post-intervention serum LH/FSH levels of 1.0–1.5 and 5 patients with serum LH/FSH levels over 1.5) will be selected for metagenomic analysis.

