### Statistical methods

Data will be analyzed using SPSS version 19.0 (SPSS 19.0, SPSS Inc., Chicago, IL, USA) by two qualified statisticians. Full analysis set (FAS), per-protocol analysis set (PPS), and safety set (SS) principles will be used to evaluate the final results. FAS is determined according to an intention-to-treat (ITT) population and includes all patients who have received at least one treatment. PPS will include all patients with good compliance who have completed the entire intervention. SS will include all patients who have received at least one intervention. The results of the measurement data analysis will be described using mean, median, 25th percentile, 75th percentile, standard deviation, maximum values, and minimum values. The comparison between the groups will be performed using the independent sample *t*-test or the Mann-Whitney *U* rank sum test according to whether the measurement data show a normal distribution and homogeneous variance. Frequency and constituent ratios will be used to describe enumeration data, and Pearson’s *χ*^2^ test or Fisher’s exact test will be used for group comparisons. Pearson correlations and Spearman correlations will be used to analyze the correlations between different indicators. All statistical tests will be considered statistically significant at *P <* 0.05 with a two-sided test. The gut microbiome will be analyzed using metagenomic analysis by BGI Shenzhen Co., Ltd (China).

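### Whether microbiota composition differs significantly between groups is left to PCA and PCoA, which use no group label and give no p-value; a distance-based test should be named

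*Protocol article*

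**What the plan says.** All places are in the protocol article.

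- **Secondary outcomes, metagenomic part (3), beta diversity.** A single sentence names the methods and their purpose. The methods: "principal component analysis (PCA) and principal coordinate analysis (PCoA) will be used to identify the beta diversity in each group". The purpose, joined to this by an 'and': "hopefully to understand whether the differences in the microbiota compositions of groups are significant".
- **Secondary outcomes, opening list.** The microbiome endpoint is "changes in gut microbiome analysis", measured before the study and after three treatment cycles.
- **Statistical methods, group comparisons.** "The comparison between the groups will be performed using the independent sample *t*-test or the Mann-Whitney *U* rank sum test". Chi-square or Fisher tests are for counts, and Pearson and Spearman correlations for pairs of indicators.
- **Statistical methods, threshold.** "All statistical tests will be considered statistically significant at *P <* 0.05 with a two-sided test".
- **Statistical methods, microbiome.** The only line names the laboratory and no test: "The gut microbiome will be analyzed using metagenomic analysis by BGI Shenzhen Co., Ltd (China").
- **Sample size.** The metagenomic subset is 10 women per arm: "5 patients with post-intervention serum LH/FSH levels of 1.0–1.5 and 5 patients with serum LH/FSH levels over 1.5".
- **Study design.** In addition, "ten healthy subjects who meet the study criteria will be recruited as the healthy control group".

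**The concern.** The sentence on beta diversity asks an inferential question (do the groups differ significantly in overall composition?) and gives it to two unsupervised ordinations. They display the directions of largest total variation among samples. They do not look for, or test, the direction in which groups differ. This is more than an unnamed detail: the method that is named does not fit the purpose stated beside it.

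The Discussion hypothesises that acupuncture works by changing gut microbiome composition, and part (3) is the only place in the metagenomic plan where whole communities are compared through a between-sample measure. With 10 women per arm, visual separation on two axes would be weak support, and no error rate would be attached to it.

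**Working it through.** The plan gives no effect size, variance, distance measure or power for beta diversity, so there is no figure to reproduce. The check is of method.

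**1. What the two methods take as input.**
- PCA: with X the centred samples-by-taxa matrix, X = U S V′ and the scores are U S.
- PCoA: with D the distance matrix and J = I − 11′/n, form B = −½ J D² J (D² taken element by element). The coordinates are its eigenvectors scaled by the square roots of their eigenvalues.

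The vector of group labels appears in neither. Relabel the women in any way and every coordinate stays the same. There is no statistic that depends on group, hence no null distribution, no p-value and no type I error rate. This holds for any data.

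**2. Whether another section supplies the test.**

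| Named in Statistical methods | What it can test |
|---|---|
| t-test, Mann-Whitney | one variable at a time, such as an alpha-diversity index or one taxon |
| Chi-square, Fisher | counts |
| Pearson, Spearman | one pair of indicators |
| Laboratory's metagenomic analysis | no test stated |

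None of these tests a multivariate composition or a distance matrix, and no permutation or distance-based test appears elsewhere in the article.

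**3. Illustration only: the listed t-test applied to ordination axes.** The protocol does not propose this. For k independent axes each tested at 0.05, the chance of at least one false positive is 1 − 0.95^k:
- k = 2: 1 − 0.9025 = 9.75%
- k = 3: 1 − 0.857375 = 14.3%

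A simulation under no group difference (assumed: 200 log-normal taxa, Bray-Curtis distance, 1,000 data sets, 199 permutations) gave:

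| Size | Any of 2 axes | Any of 3 axes | PERMANOVA |
|---|---|---|---|
| 10 v 10 | 10.8% | 15.4% | 4.1% |
| 5 v 5 | 10.8% | 15.7% | 4.3% |

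So the listed tests are not a ready substitute if used axis by axis, whereas a label-permutation test stays near its nominal 5% even at these sizes.

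**4. Whether a permutation test is feasible.** With equal groups, swapping the two labels throughout leaves the pseudo-F unchanged, so the smallest p is 2 divided by the number of arrangements.
- 10 v 10, unrestricted: C(20,10) = 184,756; smallest p = 2/184,756 ≈ 0.00001.
- Arms permuted within the two LH/FSH strata (5 v 5 in each): 252 × 252 = 63,504; smallest p = 2/63,504 ≈ 0.00003.
- LH/FSH strata within one arm, 5 v 5: C(10,5) = 252; smallest p = 2/252 ≈ 0.008 (1/252 ≈ 0.004 if the mirror arrangement is not counted).

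All lie below 0.05, so each contrast can in principle reach the threshold.

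**The case against.** The best defence is that this is a condensed article. Part (3) belongs to a six-item list of planned outputs, none of which names a test. Ordination accompanied by an unnamed group test is a plausible reading, and an analysis plan or laboratory pipeline that is not shown could supply it. The aim is also hedged by the word hopefully, and the article already discloses the small metagenomic sample as a limitation. Much of this stands and limits the weight of the point. It does not remove it: the text attaches the significance question to PCA and PCoA, and that sentence would need correcting even if a test exists elsewhere.

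A reader might infer three stronger things that the document does not support.

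- **That separation on a plot will be declared a finding.** This is a risk. The article states no such rule.
- **That composition is compared nowhere else.** Parts (1) and (4) compare composition and relative abundance at six taxonomic levels, and univariate tests can be applied there. What part (3) alone offers is the whole-community comparison.
- **That a definite amount of power is lost.** A simulation (10 v 10, 100 log-scale taxa, 400 replicates per setting) compared a Hotelling test on the first two principal components with PERMANOVA. PERMANOVA's advantage in the six settings with a true shift was 2, 23, 10, −1, 2 and 8 percentage points. The largest gap (45% against 68%) is one setting of six. The shift was built orthogonal to the main gradient, which disfavours the leading axes, and the protocol never proposes the Hotelling test. No power figure can be carried over to this trial.

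**Conclusion.** The point holds in limited form. The article gives the question of significant compositional difference to two methods that cannot answer it, and names no multivariate or distance-based test that could. This conclusion needs no assumption about the data, only that no test is specified in a document not shown.

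Its reach is modest: one part of an exploratory secondary outcome in 10 women per arm. The primary LH/FSH comparison is unaffected. The consequence for power or false positives cannot be quantified from the document; the simulated rates above rest on assumed data and illustrate the mechanism only. The change is worth making because it costs almost nothing.

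A valid test would not make the arm comparison a randomised one. The 10 women per arm are chosen by post-intervention LH/FSH, which is itself the trial's primary measure, and the arms are balanced on it by design.

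**What to change.** In part (3), or in the analysis plan:

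1. Keep PCA and PCoA as descriptive plots and state that no significance claim is made from them.
2. Base any significance statement on PERMANOVA with label permutation, on one distance fixed in advance (for example Bray-Curtis). Report R2 with the p-value, read from the upper tail at 0.05, because the pseudo-F has no two-sided form. Add PERMDISP so that unequal spread is not taken for a shift in composition.
3. Name the contrasts:
   - Study versus control, on the baseline-to-end change (which matches the stated outcome) or at end of treatment, with the baseline contrast as a check. Permute labels by woman within LH/FSH stratum, so that her two samples move together. Bray-Curtis cannot be applied to differences that may be negative, so if change is chosen with this distance, test the group-by-visit term.
   - LH/FSH 1.0–1.5 versus over 1.5 within each arm (5 v 5), the contrast closest to the aim of explaining individual differences.
   - Healthy controls as a separate contrast.
4. State that, because the women are selected on post-intervention LH/FSH, the arm contrast is exploratory and not a randomised estimate.

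Cost: one paragraph of text and a standard step on a distance matrix that PCoA already needs. No new samples, patients or visits. The downside is that, at these sizes, a separation that looks clear on a plot may prove non-significant.
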